### Intervention

The main interventions of the study include:

(a) a programme of individualised psycho-educational instruction focusing on behaviours prior to and during a illness related crisis,

(b) the distribution of an individualised crisis card containing essential information and guidelines for preventing an acute crisis or for acting properly prior to or during a relapse, and

(c) a 24-month preventive monitoring of individual risk factors of relapse or inadequate disorder-treatment-related behaviour.

All measures are provided by a personal mental health care worker (psychologist), who will be available and maintain permanent contact to the patient throughout the intervention and follow-up period of the study.

The intervention programme shall not replace the patients’ regular therapy. Rather, it is considered as a supplementary measure to give chronically mentally ill patients individual support to become more actively involved in their care. Because the programme targets an increase in the patient’s empowerment, no structured collaboration between the personal mental health care worker and the regular treatment team is intended. The regular (inpatient) treatment team is informed that a patient is participating in the study. Members of the regular treatment team, however, are not aware of the outcome of randomisation.

(a) Individualised psycho-educational instruction of study patients

Immediately after recruitment and randomisation, each study patient in the intervention group attends the initial (1–3) instruction sessions. These sessions address information on relapses in mental disorders, treatment and adequate behaviour to prevent a crisis. The sessions are scheduled prior to discharge from the index episode (inpatient stay in the study centres) and individually adapted to the specific needs, experiences and history of illness of the respective patient. The series of initial sessions aims to establish a good relationship between the patient and the personal mental health care worker who assesses and guides the patient through the phase of preventive monitoring. The issues that are addressed include: information on the course of the disorder in question and risk factors for relapses, the structure of mental health care networks and ways of optimised use of services and treatments (including psychotropic drugs).

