After discharge from the inpatient index episode, each patient is contacted every fourth week by telephone. These contacts will cover the complete follow-up period (24 months). Patients, however, are not visited at home. If the study participant does not answer the phone, the personal mental health care worker will follow-up until he/she gets through to the study patient. At each contact, the present status of study patients is assessed using the individual risk factor checklist. In order to assess service utilisation other scales are applied (instruments, see below). Monthly contacts are designed to provide a dense individual pattern of the course of the illness and the utilisation of health care services. Preventive monitoring enables detection of early signs of a crisis or a threatening relapse and offers opportunities to discuss issues or to intervene in case of problems.

It is only in emergency situations in which a patient may constitute a danger to himself or others, (e.g., if a study participant reports suicidal thoughts, but refuses to see any mental health care professional or other persons) that the personal mental health care worker will adopt measures to protect the study participant. Patients are informed that in such a situation the confidentiality agreement will be ignored. It is not intended, however, that the personal mental health care worker who maintains contact to the patient during follow-up communicates with a patient’s regular therapists or other mental health care professionals. Only if a patient explicitly desires this, may the personal mental health care worker impart information.

The individual data on the course of illness and care will be used to analyse a possible association with the major outcomes of the study. The recording of involuntary admissions to psychiatric hospitals, forensic facilities or prison terms during the follow-up period will allow analysis of the complex interdependencies between individual illness-related features and the pathways to institutionalised care in these sectors. Additionally, service utilisation data will be transformed into cost information and used to analyse the potential cost-effectiveness of the major study intervention (compared to treatment as usual in the control group).

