### Measurements

At baseline (t0) and again after 12 (follow-up t1) and 24 months respectively (follow-up t2), data on patient characteristics and health care use are gathered by means of face-to-face interviews and questionnaires. Interviews with study participants (intervention and control patients) are conducted by the members of the study staff.

Baseline assessment is scheduled upon discharge from the index episode at one of the study centres. Additional data concerning individual risk factors and service utilisation are collected during the monthly telephone contacts between the patient and his/her personal mental health care worker (intervention group).

As the overall number of questions at baseline assessment is high, a limited number of scales will be applied at the t1- and t2-follow-ups to limit the burden on patients and to comply with restricted time resources available for the interview session. Table 1 provides an overview of the measurements and the instruments used at the different time points.

**Table 1 T1:** Outcome measures

**Variables**	**Instrument**	**Time of assessment**
Sociodemographic data	Patient file; CSSRI-EU	t0, t1, t2
Utilisation of mental health care or other relevant services (Previous health care use; number and length of voluntary and involuntary psychiatric inpatient episodes; frequency and length of stays in forensic facilities, frequency of use of outpatient psychiatric care and of other services during follow-up)	CSSRI-EU	t0, t1, t2 continuously in the intervention group; every 3 months in the control group
Psychopathology	CGI; GAF; OQ- 45; BPRS	t0, t1, t2
Risk of self-harm or threat to others	Patient file; HCR-20; PCL-SV; BPRS	t0, t1, t2
Informal coercion/perceived coercion	MacArthur AES	t0
Empowerment	Empowerment-Scale	t0, t1, t2
Treatment satisfaction	CSQ-8	t0, t1, t2
Quality of life	WHO-QoL-Bref	t0
Social support	BSSS	t0
Internalised Stigma	Internalised Stigma of Mental Illness Inventory	t0, t1, t2
Self-esteem; Cognitive appraisal of stigma as a stressor; Emotional reactions to compulsory admission	Rosenberg Self-Esteem Scale; Stigma-Stress Scale; 4 items	t0

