#### Data analysis and statistical power

All major endpoints of the study will be compared between the intervention and the control group. Primary outcome of the study is the time in hospital accumulated over all involuntary inpatient stays during the 24 month period. This outcome criterion will be analysed in terms of both “time in hospital” and savings of health care budgets (“health care costs”).

As further endpoints of the study (secondary outcome criteria) changes in the perspective of the patients are assessed. Hypothesised benefits of the intervention are a reduction of institutionalised care and coercion. Lower levels of subjectively experienced coercion are supposed to be associated with a respective increase in quality of life, treatment satisfaction and level of empowerment.

To address the major research questions, the quantitative outcome data will be analysed for the whole trial across the four centres, using General Linear Models. T-tests for independent samples are applied primarily to test the comparability of the intervention and the control group. Analyses of covariance are performed to compare the intervention and the control group with respect to the primary outcome (time in hospital accumulated over all involuntary inpatient stays) and secondary outcomes (reduction in levels of subjectively experienced coercion; increase in quality of life, treatment satisfaction and level of empowerment). Age, gender, centre and other variables which show significant between-group differences are included in the GLM models as covariates. To examine which characteristics on the patient level (treatment history, diagnosis, social network, treatment adherence in the two-year follow-up) modify the outcome, we examine the effects of these variables on the outcomes of interest within the intervention group, applying regression analyses. The level of significance is set at 0.05, two-tailed.

The planned overall sample size across all centres is 400 patients, of which 200 each will be assigned to the intervention group or to the control group. So each centre is expected to contribute 100 patients (50 intervention group and 50 control group).

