### Preliminary reflections on the limitations and strength of the study

A limitation of the study may be that long-term engagement in an intensive programme such as the one proposed may be difficult for patients with serious mental disorders. A selection bias at inclusion may be expected as a result of the consent procedure and during the follow-up as a result of dropouts. An advantage of the study, however, is that patients who have previously experienced compulsory measures in psychiatry may now have a strong interest to participate in such a programme in order to avoid further compulsory admission.

To determine dropout effects, differences between patients included in the study and those not included, but eligible for inclusion (to be traced by means of the respective hospital statistics) will be analysed. Likewise, patients who finish the programme and those who drop out during follow-up will be compared with respect to psychopathological, social and health care characteristics. We thus hope to better understand which patients might qualify for such a programme and to what extent results can be generalised. If dropout analysis does not reveal any systematic bias, the results likely may be generalised for a population of mentally ill at risk for involuntary psychiatric care.

Long-term engagement (24-month preventive monitoring), on the other hand, might be a strength of this study. Advance directives alone do not necessarily impact the outcome of care, as the study by Papageorgiou et al. [12] suggests. There are several reasons attributable to peculiarities on the part of the mental health care system, as well as on the part of patient behaviours, as to why directives might be ignored. It is considered a meaningful and integral part of this trial, therefore, to follow patients after hospital discharge, all the more so as a considerable number of this patient group holds reservations towards visiting an outpatient mental health professional. In this situation, a preventive monitoring may have beneficial effects, bringing to mind betimes the patient’s individual action plan in case of a crisis and motivating them to continue treatment.

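### Involuntary stays, which make up the primary outcome, are recorded on a schedule that differs by arm; the source feeding the endpoint is not stated, leaving the comparison open to differential ascertainment

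*Protocol article*

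**What the plan says.** The section on data analysis and statistical power defines the endpoint: "Primary outcome of the study is the time in hospital accumulated over all involuntary inpatient stays during the 24 month period". The same section says it will be analysed both as time and as health care costs.

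Table 1 (Measurements) places the components of that endpoint, "number and length of voluntary and involuntary psychiatric inpatient episodes", in the service-use row. The only instrument listed in that row is the CSSRI-EU. The timing cell gives t0, t1 and t2 and then adds: "continuously in the intervention group; every 3 months in the control group".

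The text under Measurements says that study staff interview patients of both arms face to face at baseline, 12 and 24 months. It then describes interim collection for one arm: data on risk factors and "service utilisation are collected during the monthly telephone contacts between the patient and his/her personal mental health care worker (intervention group"). Under Intervention, part (c), the frequency is given: "After discharge from the inpatient index episode, each patient is contacted every fourth week by telephone". On unanswered calls it says: "If the study participant does not answer the phone, the personal mental health care worker will follow-up until he/she gets through". The Intervention section also makes clear that this same worker delivers every component of the programme.

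Hospital statistics are mentioned in the section on limitations and strengths, but for another purpose. They serve to compare included patients with eligible patients who were not included, the latter "to be traced by means of the respective hospital statistics".

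**The concern.** Two arms can be compared fairly on accumulated involuntary days only if a day has the same chance of being recorded in each. Here the interim schedule gives the arms different recall periods and different contact intensity. In one arm the collector is also the person whose programme is being evaluated. A stay forgotten, misdated or given the wrong legal status can then depend on allocation.

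Error could run either way. Closer contact may capture more stays in the intervention arm and hide a benefit. Under-recording by the worker who delivers the programme would create or enlarge one. Costs built on the same service-use data would inherit the problem.

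**Working it through.** **1. Collection by arm, as stated in the article**

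| Item | Intervention | Control |
|---|---|---|
| Common interviews | t0, t1, t2, by study staff | t0, t1, t2, by study staff |
| Interim collection (Table 1) | continuous | every 3 months |
| Interim contact rate | every 4 weeks | every 3 months |
| Interim collector | worker delivering the programme | not stated |
| Tracing rule for unanswered calls | repeated until reached | not stated |

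Contacts over 24 months: 24 × 30.44 / 28 ≈ 26 calls in the intervention arm, against 24 / 3 = 8 interim points in controls.

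**2. The plan's own sample size**

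Inputs from the section on data analysis and statistical power: means of 33 and 25 days, CV 1.25, log-normal lengths, two-sided 5% level, 80% power.

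- Log-scale SD: sqrt(ln(1 + 1.25²)) = sqrt(ln 2.5625) = 0.970.
- Log-scale effect: ln(33/25) = 0.2776.
- n per group = 2 × (1.960 + 0.842)² × 0.970² / 0.2776² ≈ 192. The exact noncentral t calculation gives 193.

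The stated 193 per group is reproduced. Equal ascertainment would not change it.

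**3. Illustration of differential loss**

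The article gives no misreporting rate, so the rates here are assumptions. Let x be the share of control days missed beyond any share missed in the intervention arm, acting as a constant factor. With true means of 33 and 25, the observed difference is 33(1 − x) − 25. Power uses 200 per arm, SD 0.970 and the log of the observed mean ratio. The last column sets both true means equal.

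| x | Observed difference (days) | Power | Chance of significance with no true effect |
|---|---|---|---|
| 0 | 8.0 | 81.5% | 5% |
| 2% | 32.34 − 25 = 7.3 | 75% | 5.5% |
| 5% | 31.35 − 25 = 6.4 | 64% | 8% |
| 10% | 29.70 − 25 = 4.7 | 43% | 19% |
| 20% | 26.40 − 25 = 1.4 | 9% | 63% |

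With no true effect, almost all of the excess significant results would point to apparent harm.

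**4. The opposite direction**

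If the intervention arm misses the extra share instead, the observed difference is 33 − 25(1 − x): 8.5, 9.25, 10.5 and 13 days at 2%, 5%, 10% and 20%. The last column of the table then applies unchanged, because the log-scale shift has the same size, but the false signals point to apparent benefit.

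**The case against.** The strongest reply is that a common schedule exists. Service use is also gathered at t0, t1 and t2 in both arms, by study staff, and the article calls the telephone data additional. Nowhere does it say that the telephone data feed the primary endpoint. A reader might infer that controls are assessed only every 3 months, or that no analysis could separate ascertainment from the treatment effect. The article supports neither. The t1 and t2 interviews allow a same-schedule comparison, at least as a sensitivity analysis.

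A reader might also infer that the result will be biased in a known direction. That is not shown, because plausible errors run both ways and no rate is given. Nor does silence establish that outcome assessment is unblinded, that controls are not pursued, or that dropout depends on arm. A condensed article may leave such details to the full protocol. Both arms also receive the same allowance to support assessments.

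These limits stand, but they do not remove the point. The unequal schedule is stated outright for the components of the primary outcome, so it is more than a missing detail. Intervention, part (c), follows its description of the monthly calls by saying that recorded involuntary admissions will be analysed and that service-use data will be costed and compared with usual care. This suggests, without stating it, that unequally collected data may enter the comparison. Even at t1 and t2, patients who have reviewed their service use every month may recall it better than controls.

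**Conclusion.** The point holds as a risk of differential ascertainment in the primary outcome and in the costs derived from it. It rests on three things in the article: the arm-dependent schedule in Table 1, interim collection by the worker who delivers the programme, and no named source for follow-up stays that is independent of arm. Neither direction nor size can be derived.

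The illustration shows only that the 8-day target is sensitive. An extra control loss of 5% to 10% would take 1.65 to 3.3 days from it and reduce power from about 82% to between 64% and 43%. These figures rest on assumed rates, the plan's log-normal model, a constant multiplicative loss and no recovery of missed days at t1 or t2. Because common interviews exist and the endpoint's source is unstated, this is something that should be fixed rather than a fatal defect.

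**What to change.** State which source defines involuntary days and make it the same in both arms. The preferred source is hospital or cantonal admission records, giving dates and legal status of every stay for every randomised patient over the same 24 months, extracted blind to allocation. The t1 and t2 interviews would supplement this for stays outside the records' coverage. The route looks practicable: the power calculation already used hospital length-of-stay data, and the plan already intends to use hospital statistics for eligible patients not included. Whether those records hold dated legal status for each stay must be confirmed.

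If records cannot be obtained, base the between-arm comparison on data collected on the same schedule in both arms by staff who do not deliver the programme, that is, the t1 and t2 interviews. In either case, keep the monthly intervention-arm data for monitoring and process description.

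The cost is a change of wording, one data extraction and possibly an ethics or consent amendment for record access in a trial already running. If costs rest on t1 and t2 alone, recall of outpatient service use lengthens to 12 months.

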#### Instruments

The instruments and scales applied in this study are widely used in international mental health care or clinical psychiatric research. All instruments are administered in their German version. The following dimensions are assessed:

##### Patient characteristics

Information regarding socio-demographic status, occupational, financial and living situation as well as clinical diagnoses is extracted from the patient file (index psychiatric episode) and supplemented by a comprehensive interview based on the Client Sociodemographic and Service Receipt Inventory CSSRI-EU [18].

##### Health care use

The CSSRI-EU is also used for a detailed assessment of the patient’s treatment history and treatment during follow-up. By means of this inventory, the frequency and lengths of (voluntary and involuntary) psychiatric inpatient episodes, the frequency and lengths of stay in forensic facilities, the frequency of use of outpatient psychiatric care, the amount and frequency of contacts to other health care professionals and the kinds and doses of psychopharmacological drugs taken are determined.

##### Psychopathology

is assessed using the Brief Psychiatric Rating Scale BPRS, extended version [19,20], which consists of 24 items, each rated on a 7-point scale based on a semi-structured interview guide.

Illness severity and global improvement or change are measured by the Clinical Global Impressions CGI [21]. To assess the patient’s global level of psychological, social and occupational functioning the Global Assessment of Functioning GAF [22] is applied as part of the clinical assessment.

Apart from clinical judgements the Outcome Questionnaire OQ-45.2 [23] is used for the patient’s self-assessment. This questionnaire comprising 45 items to be rated on a 5-point scale is designed to track the patient’s treatment response. Four domains of functioning are evaluated by the patient: symptoms of psychological disturbance, interpersonal problems, social role functioning and quality of life.

##### Risk of self-harm or threat to others

For a first screening of violent or self-harming behaviours in the past, information within the patient’s file prior to baseline consultation is checked. If the patient’s history is suggestive of such behaviours or the baseline interview brings out such behaviours, risk of self-harm or threat to others is rated by the staff members and if so, is assessed throughout the follow-up. Ratings are based on the Brief Psychiatric Rating Scale BPRS and a semi-structured interview developed by the research group Mental Health Services, CI Mannheim, based on the Violence Risk Assessment Scheme HCR-20 [24] and the screening version of the Hare Psychopathy Checklist PCL-SV [25]. The interview includes risk markers (32 items) which reflect past and current correlates of violence as well as situational factors that might aggravate or mitigate risk and are deemed to be predictors of recidivism, violence and the inability to respond to therapeutic intervention.

##### Perceived coercion / informal coercion

To assess the patients’ perceptions of coercion during their admission to psychiatric hospital, the MacArthur Admission Experience Survey AES [26] is applied (short form; 15 items). Additionally, perceptions of the fairness and effectiveness of coercive measures and methods of informal coercion are assessed [27,28]. Informal coercion includes negative pressures and threats as to the use of legal actions, as well as threats concerning the execution of payments, housing restrictions and the right to child custody. All coercion questions are presented on a dichotomous true/false scale. At t1 and t2 follow ups the MacArthur Admission Experience Scale, modified for outpatient use, will be applied.

##### Empowerment

The Empowerment-Scale [29] is used to measure self-efficacy, optimism, self-esteem and community-orientation. It consists of 28 statements on a 4-point scale that subjects can agree or disagree with.

##### Treatment satisfaction

is measured with the Client Satisfaction Questionnaire (CSQ-8; [30]). The patient’s global treatment satisfaction is assessed by the short form comprising 8 items.

